#### Post-treatment clinical assessment

Performed by a blinded rater according to the pre‐treatment clinical assessment visit on the same day of the last treatment (V7):

FMA‐UERelative grip strength measurement (vigorimetry)Stroke‐specific Quality‐of‐Life Scale (SS‐QOL)Modified Rankin Scale ScoreBarthel Index

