### Criteria for discontinuing or modifying allocated interventions {11b}

In the event that the stimulation is not tolerable for the patient, it will be discussed with the patient whether they would like to retry at a later time (within the specified 14 days after the stroke event, s. eligibility criteria) or whether the study participation will be terminated. Modifications of the intervention are not planned to be performed.

Reasons for premature termination of an individual trial subject are:DeathWithdrawal of consentPatient lost to follow‐upMajor protocol violationOccurrence of an Adverse Event or a Severe Adverse Event (e.g., seizures) that prevent the patient’s further safe participation in the trail.If, in the investigator’s opinion, continuation of the trial would be detrimental to the subject’s well‐being.pregnancyNoncompliance

The PI decides on the withdrawal of a patient from study treatment in case one of the criteria mentioned above occurs. The reason for withdrawal will be recorded in the CRF as well as in the subject’s medical records. Premature termination should be prevented as best as possible. In case a subject withdraws from further participation at their own request, the reasons/circumstances will be determined and documented. All sessions and assessments of the last trial day will be performed and documented as well as the final status of the patient. Each withdrawn patient should enter the follow-up phase. The patient will not suffer any disadvantage in case of requested withdrawal of any further study procedure participation including the follow up.. Adverse Events (AEs)/ Serious Adverse Events (SAEs) should be followed‐up as far as possible.. Patients will be contacted by phone or letter prior to follow‐up examinations. Subjects dropping out after completion of intervention therapy will not be replaced. A final assessment visit for the relevant safety data will be always offered to the patient.

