### Relevant concomitant care permitted or prohibited during the trial {11d}

During the study, all patients will receive standard conventional rehabilitation treatment including occupational therapy after TMS treatment for 40 min, 5 times per week. The treatment includes task‐oriented training that involves active participation of the affected limb and individualized motor task training. Subsequently, exercise training, including active‐assistive range of motion exercise of the affected extremity, holding, moving, releasing of cups and cubes, will be administered by the same therapists.

According to the exclusion criteria participation in competing trials or therapeutic interventions other than conventional rehabilitation treatment procedures with effect on motor recovery, will have to result in termination of study participation. Patients are informed about the regulations before giving informed consent.

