### Provisions for post-trial care {30}

There will be no special procedures following for patients that have completed the trail. Patients will be treated according to the standard of care after the termination of the study. After the last treatment, the subject enters the Follow‐up phase. For patients prematurely terminating the study for one of the above listed reasons, there will be no special follow‐up procedures. In case of a premature termination of therapy, reasons/circumstances and if applicable the final status will be documented. If the patient does not withdraw the consent for further Follow‐up, he/she should be followed‐up as planned. To those who suffer harm from trial participation (e.g., epileptic seizure, headache), the standard treatment for the symptoms that have been arisen will be provided in the hospital.

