### Outcomes {12}

#### Primary clinical endpoint

Primary efficacy endpoint is the motor performance after the intervention, as assessed by the Fugl‐Meyer assessment of the upper extremity (FMA‐UE). The upper‐extremity (UE) portion of the Fugl‐Meyer assessment (FMA‐UE, range 0‐66, 0 = no motor function, 66 = normal motor function) is the most frequently used scale to quantify post‐stroke motor recovery of the upper extremity [23] and correlates well with subjective assessment of motor function. The FMA‐UE was used as an endpoint in most of the recent high‐frequency rTMS trials in early subacute stroke patients [18–21]. For these reasons, the FMA‐UE immediately after the last treatment session was chosen as the primary outcome measure of this trial.

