### Participant timeline {13}

The study is planned to span a total duration of 42 months, between November 2022 and May 2026. The TMS intervention duration for each subject is 1 week (5 sessions per week). The maximum study duration including screening, MRI scan, TMS intervention and a 3-month follow-up measurement for each subject will be 3.5 months. The time course of events can be seen in Table 1.

**Table 1 Tab1:** Flow chart of visits and events

**Events**	**Screening (V1)**-14 days to -1 day prior 1th treatment	**Treatment (V2-6)** (treatment will be performed on 5 following working days)	**Post –treatment (V7)**^**g**^ (last treatment and post- treatment visit will be performed on the same day)	**Follow-up (V8)**^**g**^(after 3 months ± 7 days)
Study Entry				
Informed Consent (IC)	X	–	–	–
Inclusion/Exclusion Criteria	X	–	–	–
Physical and neurological examination	X	–	–	–
Medical History	X	–	–	–
Pre-treatment clinical assessment^a^	X^f^	–	–	–
TMS and EEG measurement^b^	X^f^	–	–	–
MRI^c^	X	–	–	–
Randomization^d^	X	–	–	–
TMS and physiotherapy sessions	–	X	–	–
Post-treatment assessment^a^	–	–	X	–
Post-treatment follow-up assessment ^e^	–	–	–	X
Adverse Events	–	Start of study treatment or after first treatment and until 7 days after discontinuation from treatment		

^a^pre & post treatment assessment and tests: Fugl‐Meyer Assessment upper extremity (FMA-UE); grip strength; SS‐QOL; Rankin Scale; Barthel Index. For screening, FMA-UE and grip strength should be repeated within 3 days prior first treatment (V2), if the screening was done earlier

^b^Each center will send the EEG raw (32‐channel) data to the coordinating center. It is sufficient that appropriate data from a standard EEG measurement is available. This can also be from an examination before screening

^c^MRI is not mandatory for inclusion, but a sufficient imaging should be available before start of treatment (please

see section “screening visit V1” for more details)

^d^in case of eligibility the randomization will take place at the end of the screening

^e^post treatment follow-up assessment and tests: FMA-UE; grip strength; SS‐QOL; modified Rankin Scale; Barthel Index; number of days as an inpatient during the 3 months after the intervention

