## Statistical methods

### Methods and analyses {20a, 20b, 20c, 21b}

The primary population is the intent‐to‐treat population. This population is defined as all randomized patients with Baseline measurement of the primary endpoint (inclusion criterium). The primary analysis will be done as Baseline‐adjusted analysis of covariance, adjusted for study center with a type 1 error of 0.05 (two‐sided for pairwise comparisons) with primary endpoint FMA‐UE measured at the last therapy visit. The study arm will be coded as a three level factor and in the first step an F‐Test for the overall null hypothesis (all three means are equal) vs. the alternative (at least two measures are different) will be done. If this test is significant, all three pairwise comparisons will be performed without correction for multiple testing. If the F‐Test is not significant, p‐values for pairwise comparisons will be calculated but have to be interpreted descriptively. In the case of a significant result (for the F‐Test) in this step, following the principle of testing hierarchically ordered hypotheses, the same strategy will be applied for follow‐up after three months. For the parameters of interest (effects within study arms and their differences between study arms) two‐sided 95% confidence limits will be calculated. In case of relevant imbalances between study arms regarding known prognostic factors, sensitivity analyses will be done adjusted for these factors. Analogous methods will be applied for the analysis of secondary endpoints (proportional odds model for ordinally scaled variables, logistic regression for binary variables, if possible baseline adjusted). Even though p‐values will be reported, all results have to be interpreted descriptively. Descriptive analyses will include means, standard deviations, and ranges for continuous normally distributed data. Medians and interquartile ranges will be calculated for non‐normally distributed data. Nominal, especially binary variables will be described using absolute and relative frequencies. Additionally, we will present line listings for AEs/SAEs. Missing values of primary and secondary endpoints will be imputed multiply using the method of Rubin. Predictor variables will be age (years), gender, study center and Baseline, which will be available in the intent‐to‐treat population (inclusion criterion). We will use 500 imputation samples; the seed will be the calendarial date of the first programming of the analysis program. An interims analysis is not planned. Exploratory subgroup analyses will be done for gender. Before breaking the code of the randomization a statistical analysis plan will be produced. Deviations from this plan will be documented and justified.. In case of premature termination of study centers or severe imbalance of prognostic factors between study centers, a sensitivity analysis non‐stratified for study centers will be presented.

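### The primary FMA-UE is timed by the last treatment actually given, and the rules on stopping do not secure an assessment at the planned end of treatment for patients who stop early

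*Protocol article*

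**What the plan says.** **Timing of the primary endpoint.** In Methods and analyses {20a, 20b, 20c, 21b} the primary FMA-UE is the value "measured at the last therapy visit". In Primary clinical endpoint it is the FMA-UE that "immediately after the last treatment session was chosen as the primary outcome measure of this trial". Post-treatment clinical assessment and Table 1 place V7 on the day of the final treatment. The schedule in Table 1 is "treatment will be performed on 5 following working days" (V2 to V6), and randomization comes before it, at the end of screening.

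**Stopping.** Criteria for discontinuing or modifying allocated interventions {11b} gives a patient who cannot tolerate stimulation two outcomes: a later retry within the 14-day window, or the end of study participation. It lists noncompliance and major protocol violation among the reasons for premature termination, then describes the decision as withdrawal from study treatment. It adds: "All sessions and assessments of the last trial day will be performed and documented as well as the final status of the patient". It also says "Each withdrawn patient should enter the" follow-up phase. Relevant concomitant care {11d} says that competing trials, or interventions affecting motor recovery other than conventional rehabilitation, "will have to result in termination of study participation". Provisions for post-trial care {30} says: "For patients prematurely terminating the study for one of the above listed reasons, there will be no special" follow-up procedures. The same paragraph says that patients who do not withdraw consent for follow-up should be followed as planned.

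**Analysis set.** All randomized patients with a baseline FMA-UE are analysed, and missing endpoints are multiply imputed.

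**The concern.** The primary analysis set is fixed at randomization, but the time of the primary measurement depends on something that happens afterwards: when treatment ends. In a population that is recovering, a value taken several days early will tend to be lower than one taken on the planned day. If such a value is not used, the outcome is missing and has to be imputed, although the patient could have been assessed.

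Either route could differ by arm. Stopping may depend on tolerability, which can differ between active and sham stimulation. The staff who deliver treatment know the condition, and the listed reasons for termination include the investigator's opinion. Sites reading {11b}, {11d} and {30} could also reasonably act differently on who is still assessed. The 3-month FMA-UE is the next step in the hierarchical testing, so patients removed during follow-up affect a tested endpoint as well.

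**Working it through.** **1. The plan's own figures.** From Sample size {14}: SD 12, effect size 0.67, middle arm 0.335, R-squared 0.2, 36 evaluable per arm.
- Powered difference: 12 × 0.67 = 8.04 points.
- Overall F-test: noncentrality 36 × (0.335² + 0² + 0.335²) / 0.8 = 10.1. Power is 80.8%, and 36 is the smallest n per arm that reaches 80%.
- Pairwise test: 0.67 / √(0.8 × 2/36) = 3.18, power 88.0%.
- Recruitment: 144 × 0.8 = 115.2 evaluable against 108 needed, which leaves about 7 for the center and baseline degrees of freedom.

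The sample size reproduces, so the point concerns only who is measured and when.

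**2. The passages side by side.**

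| Patient | Primary time point (V7) | 3 months (V8) |
|---|---|---|
| Completes five sessions | Uniform, day of fifth session | Planned |
| Stops early, intolerance, no retry | Participation ends ({11b}); at most last-trial-day assessments | Conflict within {11b}, and between {11b} and {30} |
| Stops early, other listed reason | At most last-trial-day assessments ({11b}) | Same conflict |
| Delayed retry | Moves with the last treatment | Moves with the last treatment |
| Competing trial or non-conventional motor therapy | Participation ends ({11d}) if before V7 | {11d} against {11b} and {30} |

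The lines that support continued assessment refer to the follow-up phase. Under {30} that phase begins after the last treatment, and its only scheduled visit is V8. The final visit that {11b} always offers is described as being for safety data. Nothing in the article brings an early stopper back for FMA-UE on the planned day of the fifth session.

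**3. How many patients.** The article does not say how many will stop early.
- Intolerance in a comparable trial ({11c}): 4/157 = 2.5%; 144 × 4/157 = 3.7, about 4 patients.
- Average all-cause dropout in the cited trials ({15}): 144 × 0.171 = 24.6, about 25.
- Planning allowance ({14}): 144 × 0.20 = 28.8, about 29.

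The last two are losses for any reason, so they are upper bounds for a visit about one week after treatment starts.

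**4. Possible bias if early values are used.** Two inputs are assumptions, not in the article: recovery of 0.5 to 2 points per day, and a 10-percentage-point difference between arms in early stopping.
- A stop after session 2 is three sessions short. Taken as 3 days: 3 × 0.5 = 1.5 to 3 × 2 = 6 points low per patient.
- Bias in the contrast: 0.10 × 1.5 = 0.15 to 0.10 × 6 = 0.6 points.
- Relative to 8.04: 0.15/8.04 = 2% to 0.6/8.04 = 7%.
- Plausibility: 10% of 48 is 4.8 more early stops in one arm than in another, which exceeds the 3.7 expected in the whole trial at 2.5%. If all 4 fell in one arm, the bias would be 4/48 × 1.5 = 0.125 to 4/48 × 6 = 0.5 points.

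**The case against.** The strongest reply is that the article already says most of what is wanted. Under {11b} withdrawn patients should enter follow-up, and under {30} they should be followed as planned unless they withdraw consent. Read together, the line about no special follow-up procedures can simply mean nothing beyond the scheduled visits. A reader might infer that the plan removes these patients outright; the article does not support that. What remains is that {11d}, and the intolerance sentence in {11b}, end study participation in so many words, and that the reassuring lines reach V8 but not V7.

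A second reply is that the early-value scenario is inferred. The last-trial-day sentence follows directly on patients who leave at their own request, where an exit assessment saves data, and no passage says that the value enters the primary analysis. That is fair: the article leaves open whether it is used or imputed over. But if the sentence covers only those patients, other early stoppers have no FMA-UE provided for at all.

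Third, {11d} exempts conventional rehabilitation. A reader might infer that poor recoverers who seek more therapy would be dropped and their 3-month values imputed from better recoverers. The most obvious recourse is permitted, and no frequency is given for the rest, so that inference is not supported.

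Fourth, the handling of an exit value can be left to the analysis plan. True of the handling, but an analysis plan cannot recover an assessment that was never made.

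**Conclusion.** The point stands in a limited form. The primary FMA-UE is anchored to the last treatment received, no passage secures an assessment at the planned end of treatment for patients who stop early, and the passages on ending participation conflict with those on continued follow-up.

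It does not follow that outcomes are measured at unequal times across the trial: V7 is uniform for everyone who completes five sessions, so only early stoppers and delayed retries are affected. Nor does it follow that 20% of patients are affected by these clauses, since that figure allows for loss of every kind. The likely number is uncertain, from about 4 to at most about 29 of 144. The bias is probably small, 0.15 to 0.6 points on an assumed recovery rate and an unsourced arm difference. It deserves correction because the missing outcomes are avoidable and cannot be repaired at analysis. No change to the sample size follows.

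**What to change.** 1. Reconcile {11b}, {11d} and {30} so that ending study treatment, for whatever reason, does not end outcome assessment: V7 and V8 are carried out unless the patient withdraws consent for follow-up. This concerns assessment only and leaves the grounds for stopping treatment untouched.
2. In Methods and analyses, define the primary endpoint as FMA-UE on the planned V7 day, meaning the originally scheduled day of the fifth session, for every randomized patient whatever treatment was received. Align Primary clinical endpoint and Post-treatment clinical assessment with it.
3. State how the primary time point is handled for a patient who has a delayed retry under {11b}.
4. Use an FMA-UE taken at early exit only as a predictor in the imputation model, not as the primary value.

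The cost is a change of wording and a few blinded assessments of patients who have stopped treatment, at visits already in the schedule.

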### Sample size {14}

It is planned to recruit 144 patients for the study. This corresponds to a recruitment rate of approximately 10 patients per study site and year. The primary objective is to establish whether personalized stimulation (Experimental Condition) is superior to non-personalized stimulation (Control Condition 1) and sham stimulation (Control Condition 2) regarding differences in FMA-UE at the end of intervention. A mean FMA-UE at baseline of 33 ± 12 [31] is expected. From the guideline [24] a minimal clinically significant improvement of 12 points on FMA-UE is derived, which leads to an effect size of 1.0. However, an effect size of 0.67 instead of 1.0 will be conservatively assumed, as a large placebo effect in the sham condition might be observed, and also in the non-personalized stimulation condition. The analysis will be done as an analysis of covariance (baseline adjusted) with overall F-test for the factor “study arm”. If the F-test is significant, according to the closed testing procedure (Hochberg Tamhane, Multiple Comparison Procedures, New York, 1987) no adjustment for multiple testing will be necessary for pairwise comparisons in the three arm situation. Assuming normal distribution of the primary outcome measure and an R-squared of 0.2 for the covariate (baseline FMA-UE) 36 evaluable patients per arm will be needed and, thus, 108 evaluable patients in total for the F-test (type 1 error 0.05, power 80%). This is based on the worst case scenario of an effect size for non-personalized stimulation = 0.67/2 = 0.335. Thus, on the one hand, it is ensured that in the case of unexpectedly positive results of the non-personalized stimulation, there will be enough power to proceed to subsequent pairwise comparisons. On the other hand, if standardized differences between study arms of 0.67 hold, there will be a power of 88% to confirm these differences (type 1 error 0.05, two-sided). To adjust for degrees of freedom for center, baseline, and 20% dropouts, 144 patients will be included, i.e., 48 per study arm. The sample size calculation was performed by PASS 2020.

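### The step to the 3-month tests depends only on the post-treatment F-test, so it is not the hierarchical procedure claimed: error over both visits can reach about 7–10% under a partial null, and the plan contradicts itself on whether the 3-month tests are formal

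*Protocol article*

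**What the plan says.** The Methods and analyses section sets a baseline-adjusted analysis of covariance of FMA-UE at the last therapy visit, "adjusted for study center with a type 1 error of 0.05", starting with an overall F-test of the three arms. "If this test is significant, all three pairwise comparisons will be performed without correction for multiple testing". The Sample size section gives the reason: under closed testing "no adjustment for multiple testing will be necessary for pairwise comparisons in the three arm situation".

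The Methods section then moves to 3 months. The condition is "In the case of a significant result (for the F‐Test) in this step", and what follows is that, "following the principle of testing hierarchically ordered hypotheses, the same strategy will be applied" at the 3-month follow-up. No pairwise rejection is required and no alpha is divided between the visits.

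Three further statements bear on the status of these tests. The Secondary endpoints section lists 3-month FMA-UE as secondary. The title and the Trial design section call the trial exploratory. The Methods section says, directly after the sentence on secondary endpoints, that p-values will be reported but all results are to be read descriptively.

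**The concern.** A fixed hierarchy may pass the full 0.05 to a later hypothesis only if every earlier hypothesis in the chain has been rejected. Here the chain passes through the global null alone. The F-test can be significant solely because active stimulation differs from sham, which the Background section treats as a likely benefit of conventional rTMS. Personalized versus non-personalized, named in the section on the choice of comparators as the main comparison, may then fail post-treatment and still be tested again at 3 months at an unadjusted 0.05. A positive 3-month result could be reported as protected by a hierarchy when it is not.

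**Working it through.** **Inputs.** From the Sample size section: 36 evaluable patients per arm, R² of 0.2 for baseline, type 1 error 0.05, effect 0.67 for personalized ("an effect size of 0.67 instead of 1.0 will be conservatively assumed") and 0.335 for non-personalized ("worst case scenario of an effect size for non-personalized stimulation = 0.67/2 = 0.335"). The between-visit correlation of the baseline-adjusted outcome, rho, is not in the document and is assumed to lie between 0 and 0.9. Arm means are given in SD units in the order sham / non-personalized / personalized.

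**The plan's own figures.** The noncentrality of the F-test is n × (sum of squared deviations of the means) / (1 − R²).
- Means 0/0.335/0.67: 36 × (2 × 0.335²) / 0.8 = 10.10. With 2 and 104 degrees of freedom the power is 80.8%; 35 per arm gives 79.5%. The stated 36 per arm is reproduced.
- Pairwise: d = 0.67/√0.8 = 0.749, noncentrality 0.749 × √18 = 3.18, power 88.0%. The stated 88% is reproduced.

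**One visit.** With two arms equal and the third different, the only true null is one pairwise hypothesis, tested at 0.05. With all arms equal, the F-test itself holds 5%. Simulation gives 5.0% for the primary family, so the closed-testing statement is correct at one visit.

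**Both visits, by hand.** Take equal active arms at 0.67 above sham. The noncentrality is 36 × (2/3 × 0.67²) / 0.8 = 13.47, and the F-test is significant in 91% of trials. A false post-treatment finding needs a significant F-test, so at rho = 0 the error over both visits is about 0.05 + (0.91 − 0.05) × 0.05 = 0.093. If the F-test is almost always significant, the limit is 1 − 0.95² = 9.75%.

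**Both visits, by simulation** (300,000 trials per setting, 36 per arm, same means at both visits). The table shows the chance of a false personalized versus non-personalized finding at either visit, with means 0/0.67/0.67:

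| rho | Error over both visits |
|---|---|
| 0 | 9.3% |
| 0.5 | 8.8% |
| 0.7 | 8.1% |
| 0.9 | 7.1% |

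With means 0/1/1 the error is about 9.8% at rho 0 and about 8.3–8.5% at rho 0.7. With means 0/0.335/0.335 the F-test is significant in only 35% of trials, and the error is 5.2–5.6%. With all arms equal the familywise error is 5.0%.

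**A stricter gate.** Suppose the 3-month step requires both personalized comparisons to be significant post-treatment, and non-personalized versus sham is descriptive. If either personalized null is true post-treatment, the gate opens only after a false rejection, which the first closed test already limits to 5%. If both are false, only the 3-month closed test can err, again at most 5%. Simulation agrees: 5.0% with means 0/0.67/0.67. If non-personalized versus sham stays formal, this gate does not protect it: with means 0/0/0.67 the error is about 6.5–8.8%. Gating each 3-month comparison only on its own post-treatment counterpart is also insufficient: it still gives about 6.5–9.0% when one pair of arms is equal post-treatment and all arms are equal at 3 months.

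**How often the gate opens.** In the sizing scenario 0/0.335/0.67, the F-test gate opens in 81% of trials and the stricter gate in 34%.

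**The case against.** The strongest reply is that nothing confirmatory depends on the 3-month result. The trial is exploratory, 3-month FMA-UE is secondary, the Methods section asks for descriptive reading, and the Discussion makes a follow-on confirmatory trial conditional on the primary endpoint only. On that view an omnibus gate to a later visit is a reasonable trade-off. This stands as a limit on the weight of the point: the primary family keeps its 5%, and a result at 3 months alone triggers no stated decision.

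It does not settle the matter. The same section reserves descriptive reading of the pairwise p-values for a non-significant F-test, which implies formal inference when the F-test is significant, and it names a hierarchical principle for 3 months. If everything is descriptive, that principle has no function; if it has one, the gate does not deliver it.

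A reader might also infer that the plan's familywise error is 8–10% in general, or that "all three pairwise comparisons will be performed without correction for multiple testing" is itself a mistake. Neither is supported. The excess needs a true pairwise null together with a large difference from the third arm. It nearly vanishes at the 0.335 that the plan uses for the non-personalized arm, and shrinks as rho rises. Unadjusted pairwise tests after a significant F-test are sound for three arms at one visit.

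**Conclusion.** The point holds in a limited form. The hierarchical label does not fit a gate that rests on the F-test alone, and the plan contradicts itself on whether the 3-month tests are formal. Error over both visits can reach about 7–10% under a partial null. At the plan's effect of 0.67 for both active arms it is 9.3% to 7.1% for rho from 0 to 0.9, against 5.0% when all arms are equal. These figures assume 36 evaluable patients per arm, R² of 0.2, normal outcomes and the stated range of rho. The primary analysis and the sample size are unaffected.

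**What to change.** Choose one of two changes. The plan schedules a statistical analysis plan before the randomization code is broken, so either can be fixed there.

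(a) Drop the reference to hierarchically ordered hypotheses and state that all 3-month FMA-UE p-values are descriptive. This matches the exploratory label. It costs any formal claim at 3 months.

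(b) If formal 3-month inference is wanted, state: 'FMA-UE at 3 months is tested (F-test, then pairwise, each at 0.05) only if personalized versus non-personalized and personalized versus sham are both significant post-treatment. Non-personalized versus sham is descriptive at both visits. Otherwise all 3-month p-values are descriptive.' State also that the general sentence on descriptive reading does not apply to these tests. Error for the personalized comparisons is then at most 5%. The cost is one planned formal comparison, and a 3-month step that opens in about 34% instead of 81% of trials under the sizing scenario. Requiring all three post-treatment comparisons to be significant would keep all three formal at 5%, but adds a further condition to the gate.

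### The multiple-imputation model omits study arm, so imputed FMA-UE values carry no arm difference and every arm contrast shrinks by about the missing fraction

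*Protocol article*

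**What the plan says.** All of the following is in the protocol article.

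- **Imputation** (Methods and analyses, under Statistical methods): "Missing values of primary and secondary endpoints will be imputed multiply using the method of Rubin". The predictors are then named: "Predictor variables will be age (years), gender, study center and Baseline". The number of imputations is fixed too ("We will use 500 imputation samples"), as is the rule for the seed. The predictors are justified by being available for everyone in the intent-to-treat population.
- **Analysis model** (same section): a baseline- and center-adjusted ANCOVA of FMA-UE at the last therapy visit. "The study arm will be coded as a three level factor", and an overall F-test comes first. If it is significant, the three pairwise comparisons follow, and then the same strategy at three months. The primary population is everyone randomized who has a baseline FMA-UE, so patients with a missing outcome enter through the imputed values.
- **Sample size {14}**: "an effect size of 0.67 instead of 1.0 will be conservatively assumed", with a worst case in which the "effect size for non-personalized stimulation = 0.67/2 = 0.335". This gives 36 evaluable patients per arm for 80% F-test power, and 88% power for a pairwise difference of 0.67. On dropout: "To adjust for degrees of freedom for center, baseline, and 20% dropouts, 144 patients will be included", which is 48 per arm.

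No section says that imputation is carried out within arm.

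**The concern.** An imputation model should contain at least the variables of the analysis model that uses its output. Here it lacks the one variable under test. Each missing FMA-UE is drawn from a distribution pooled over the three arms, so the imputed rows are built with no arm difference and then mixed with observed rows that may have one. The estimated differences are pulled toward zero.

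The F-test is the gate to the pairwise comparisons and to the three-month test, so lost power there affects everything that follows. The estimates and confidence limits matter as well, because the Discussion says that confirmation of the main hypothesis will lead to a confirmatory trial. An understated or missed effect would misinform that decision.

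**Working it through.** **1. The plan's own figures.** Inputs from Sample size {14}: means 0, 0.335 and 0.67 SD, R² = 0.2 (residual variance 0.8), α = 0.05.

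- F-test noncentrality = n × (0.335² + 0² + 0.335²)/0.8 = 0.2806 n. At n = 36 this is 10.1 and power is 0.808. At n = 35 power is 0.795. So 36 per arm is reproduced.
- Pairwise: 0.67/√0.8 = 0.749, times √(36/2) gives 3.18, and power is 0.88. So 88% is reproduced.
- 108/0.8 = 135. The further 9 patients up to 144 fit the stated allowance for degrees of freedom.

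The sample size itself is sound.

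**2. Shrinkage from imputing without arm.** Let f be the fraction missing in each arm, μₖ the adjusted mean of arm k, and μ̄ the mean pooled over arms. Imputed values centre on μ̄, so the completed-data mean of arm k is (1 − f)μₖ + fμ̄. The difference between arms j and k is then (1 − f)(μⱼ − μₖ). This needs similar f in each arm and missingness unrelated to outcome given the covariates. With unequal fractions the contrasts still shrink, but by different amounts.

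For a true 0.67 SD, or 0.67 × 12 = 8.04 points if the baseline SD of 12 also applies to the outcome:

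| f | SD units | Points |
|---|---|---|
| 2.5% | 0.653 | 7.8 |
| 5% | 0.637 | 7.6 |
| 10% | 0.603 | 7.2 |
| 17.1% | 0.555 | 6.7 |
| 20% | 0.536 | 6.4 |
| 24% | 0.509 | 6.1 |

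The 17.1% and 24% are the average and the highest dropout given in Recruitment {15}. The 2.5% is the intolerance dropout given under adherence. The 20% is the planned dropout.

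**3. Simulation.** Settings: 48 per arm, 6 centers, R² = 0.2, values missing completely at random, normal-model imputation and Rubin pooling. The main set used 1,500 trials per scenario and 50 imputations (not the planned 500); another used 1,000 trials and 30 imputations. Ranges span the separate simulations. Power is shown without → with arm in the imputation model.

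| f | Estimate of 0.67, without arm | F-test power (0/0.335/0.67) | Power, pairwise 0.67 |
|---|---|---|---|
| 2.5% | 0.65–0.66 | 86% → 88% | 92–94% → 92–95% |
| 5% | 0.63–0.64 | 83–86% → 87–89% | 90–92% → 93–94% |
| 10% | 0.60 | 76–80% → 84–87% | 87% → 90–91% |
| 17.1% | 0.54–0.56 | 64% → 81–83% | 77–79% → 90–91% |
| 20% | 0.52–0.54 | 53–58% → 79–80% | 73–76% → 87–88% |

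**4. Standard errors and type 1 error at 20% missing.** Without arm, the mean Rubin standard error is 0.212, but the estimate's actual SD is 0.169. The actual SD has shrunk along with the estimate (0.80 × 0.211 = 0.169), and the standard error has not. With arm the two agree (0.212 and 0.211). The ratio of estimate to standard error falls from 0.671/0.212 = 3.17 to 0.531/0.212 = 2.50. Under the null the F-test rejects 1.0% without arm and 4.5% with arm.

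**The case against.** **The 20% is overall dropout.** Recruitment {15} describes the cited rates as loss to follow-up for any reason. The primary FMA-UE is taken on the day of the last of five consecutive working-day sessions. The discontinuation section asks that last-day assessments be done and that withdrawn patients enter follow-up. Missingness at the primary visit may therefore be well below 20%; the 2.5% intolerance figure covers one cause only and is a floor. This stands. A reader might infer that the trial will in any case lose most of its power margin. The documents do not support that: at 5% missing or less, power stays above the planned 80% and 88%.

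**The 0.335 pairwise contrast.** Power for that single contrast at 20% missing is about 17% without arm and 34% with it, and a reader might take this as the plan's worst case. It is not. The worst case in the sample-size section concerns the overall F-test, and no pairwise power is claimed for 0.335.

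**Other variables off the list.** A reader might count the motor-threshold stratum and the FMA-UE at the other visit as equal defects. The stratum is not in the stated analysis model, so its omission creates no mismatch. The other visit would be an auxiliary predictor that may gain precision. No bias has been shown for either.

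**Direction.** The error is conservative and the trial is labelled exploratory. There is no false-positive risk, and the harm is confined to understated or missed effects. The article does not, however, present the omission as deliberate conservatism.

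**Missingness mechanism.** If patients who stop stimulation early are the ones missing, giving them the full arm effect could overstate theirs. This limits the exact (1 − f) factor. It is no reason to build in a null difference without saying so.

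**A later analysis plan.** One is promised before unblinding and could add arm. It might also be said that arm is implied. But the article gives an explicit list, and arm meets its stated criterion of being available for everyone in the population.

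**Conclusion.** The stated imputation rule is wrong for the stated primary analysis. Followed as written, it shrinks each arm contrast to about (1 − missing fraction) of its true value and overstates the standard errors. This assumes similar missingness across arms and missingness unrelated to outcome given the covariates.

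The size depends on a fraction that the article does not give. The effect is slight at 2.5–5% missing. At 10% the F-test power is 76–80%, at or just below the planned 80%. At 20%, the rate for which 144 patients were chosen, it is 53–58%, and putting arm into the model restores 79–80%. The three-month FMA-UE uses the same imputation model and is likely to have more missing values, so the upper part of the range is most relevant there. Type 1 error is not inflated.

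**What to change.** Add study arm, as a three-level factor, to the predictors of the imputation model, or impute separately by arm, for the primary and the secondary endpoints. Put this in the statistical analysis plan before the randomization code is broken, and record it as a correction to the published list.

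Optionally, add the FMA-UE at the other post-baseline visit and the motor-threshold stratum as auxiliary predictors.

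The cost is one sentence and one model term. No patients or data are added.
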